### Biomarkers

Biomarker discovery and validation is a critical aim of the medical and scientific community.^33^ Biomarkers can be used as an objective assessment tool for health, performance, recovery and talent identification in elite sport. Among the most critical hormones for athletes seem to be cortisol, testosterone, dehydroepiandrosterone and immunoglobulin-A (Ig-A). However, testosterone to cortisol (T:C) ratio is considered to be more sensitive to training stress than either measure alone,^33^ as several studies report poor performance outcomes and suboptimal training adaptations in athletes with a low T:C ratio.^34 35^ However, to the best of the authors’ knowledge, no previous work has examined the use of biomarkers for injury prevention, recovery after an injury or identification of individuals at increased risk.

Given all of the above, there is a need for better health surveillance, load monitoring and support services with an emphasis on injury/illness prevention and rehabilitation.^36^ As DC athletes have a wider variety of loads that pose greater psychophysiological strain to them, they could also be at an increased risk for injury/illness. Therefore, more comprehensive monitoring of potential risk factors in this specific population is warranted. It is not yet known, but important to determine how much of overall load can an athlete withstand before injury/illness occurs. Thus, the primary aim of this study is to determine how specific physical, psychosocial and DC loads affect the occurrence of injuries and illnesses in elite handball players and how much of a variation in the athlete’s load leads to an occurrence of an injury/illness. A secondary aim is to determine the association between objective and subjective measures of stress as well as examine the benefits of certain biomarkers to monitor stress, load and injury/illness occurrence in athletes.

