**Figure 1 F1:**
[figure not shown]
Assessment plan. LESCA, Life Events Survey for Collegiate Athletes.

**Table 1 T1:** Questionnaires and tests

Test/questionnaire	Outcome	Purpose
**SDSCQ**	Age, sex, level of education, sport, years of training, player position, previous injuries	General information about the athlete
**Anthropometry**	Body height (cm), body weight (kg)	Measure of basic anthropometric characteristics of an athlete
**LESCA**	Major life events score	Measure of life stress
**OSTRC**	Weekly health problems (acute and overuse injuries, illnesses), measured as prevalence and incidence and severity as OSTRC-severity score and time-loss days	Identifying health problems
**Weekly load and stress**		Monitoring of athlete’s load
	Training load in hours	
	Competition load in minutes	
	Academic load in hours	
	Work load in hours	
	Average daily sleeping hours	
	Perceived stress on scale 1–10	
**Blood biomarkers**		Monitoring of stress/insufficient recovery and/or health problem risk
Cortisol	Cortisol values in nmol/L	
Free testosterone	Free testosterone values in pmol/L	
Ig-A	Ig-A values in g/L	
	Free testosterone: cortisol ratio	

LESCA, Life Events Survey for Collegiate Athletes; OSTRC, Oslo Sports Trauma Research Center Questionnaire on Health Problems; SDSCQ, Sociodemographic and Sports-Career Related Questionnaire.

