#### Blood biomarkers

There will be three to five measurement timepoints for biomarker sampling, according to the training (preparatory period, competitive period, off-season period) cycle. The athletes will be tested under similar conditions every time, after a rest day (refrainment from intensive training the day before blood collection), between 7:00 and 10:00 in the morning.

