### Statistical analysis

Statistical analysis will be performed using standard statistical software (SPSS V.27.0, IBM, Armonk, New York). Descriptive statistics will be used for all variables. Normality of data distribution will be assessed using the Shapiro-Wilk test. In case of non-normally distributed data, non-parametric statistics will be used, otherwise, the statistics for normally distributed data will be used. The data will be analysed using a logistic regression model to properly account for the dependency induced by the repeated observations over time within each subject. Main effect of all dependent variables on injury/illness occurrence will be studied using repeated measures analysis of variance (ANOVA) with time (preparation period vs competition period vs off-season period) as within factor, while group (injured/ill vs healthy) as between factor. Where significant effects will be found for group, time effects or two-way interactions, pairwise comparisons will be used to address the significant differences for each variable independently. For comparison of the groups, we will use independent t-test. The magnitude of effect for all dependent variables will be reported as partial eta squared (η^2^). In addition, *Cohens’ d* (ES) will be used to assess magnitude of difference between groups. Furthermore, regression analysis will be used to assess predictive power of individual parameters to identify injury/illness occurrence. For the correlation of subjective measures of stress with the objective measures, bivariate correlation will be used. Additionally, Bland-Altmann analysis will be used (low/high stress normative values) as previously recommended.^42^ Furthermore, receiver operating characteristic (ROC) curve analysis will be used for defining the cut-off values. Hypotheses will be accepted or rejected at p≤0.05.

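### Blood may be drawn at any point in a three-hour morning window and no named analysis uses draw time: this weakens the secondary biomarker analyses and could confound them if timing differs by club, period or group

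*Protocol article*

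**What the plan says.** The Blood biomarkers section plans "three to five measurement timepoints for biomarker sampling", spread over the training cycle. It sets the sampling conditions in one sentence: "The athletes will be tested under similar conditions every time, after a rest day", at a clock time "between 7:00 and 10:00 in the morning". No narrower time is set for a player, a team or a visit.

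Table 1 lists the outcomes as absolute levels and a ratio, among them "Cortisol values in nmol/L" and "Free testosterone: cortisol ratio". It gives their purpose as monitoring stress, insufficient recovery and the risk of health problems.

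The biomarkers serve the secondary aim. The Introduction (Biomarkers) says: "A secondary aim is to determine the association between objective and subjective measures of stress", and adds the usefulness of biomarkers for monitoring load and injury or illness.

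Statistical analysis names the methods. One is "For the correlation of subjective measures of stress with the objective measures, bivariate correlation will be used". Others are a repeated measures ANOVA with period as the within factor and injured/ill versus healthy as the between factor, independent t-tests between groups, and ROC curves for cut-offs. None of these is described with a term for time of draw.

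**The concern.** Cortisol is commonly taken to decline through the morning. If it does so here, one player sampled at the start of the window in one period and at the end in another will show a change in cortisol, and in the ratio, that has nothing to do with stress or recovery.

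The consequence depends on how draw times arise:

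- **Timing unrelated to stress, group or period.** It is added noise. A true association with perceived stress looks weaker than it is, and a threshold in nmol/L means different things at different clock times.
- **Timing that differs by club, period or injury status.** The timing difference enters the period or group comparison and can be read as a biomarker effect.

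At stake is whether the secondary aim can tell that these biomarkers track stress and risk. The primary aim, on loads and the occurrence of injury or illness, does not use the blood samples.

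**Working it through.** **Inputs from the article**
- Window: 10:00 − 7:00 = 3 h (Blood biomarkers).
- Sample size: 134/(1 − 0.10) = 148.9, rounded up to 149 (Participants and sample size). The article's figure reproduces. It does not concern biomarkers and is used only in step 4.
- The article gives no figure for the slope of cortisol, its spread, or an expected biomarker effect, so there is no stated biomarker figure to reproduce.

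**Assumptions (not in the article)**
- ln(cortisol) falls linearly by s = 0.08 to 0.15 per hour within the window.
- The between-player SD of ln(cortisol) is σ = 0.2 to 0.3.

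**1. Difference across the window**
The ratio of the 10:00 value to the 7:00 value is exp(−3s).
- s = 0.08: exp(−0.24) = 0.79, a fall of 21%.
- s = 0.15: exp(−0.45) = 0.64, a fall of 36%.

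If testosterone stays flat, the free testosterone:cortisol ratio rises by exp(3s) − 1, that is 27% to 57%. The rise is smaller if testosterone also falls.

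**2. Draw time unrelated to anything else**
Take draw times as uniform over 3 h. Their SD is 3/√12 = 0.866 h, which adds an SD of 0.866s to ln(cortisol). A true correlation is multiplied by σ/√(σ² + (0.866s)²).
- Worst case, s = 0.15 and σ = 0.2: added SD 0.130; 0.2/√(0.0400 + 0.0169) = 0.84.
- Best case, s = 0.08 and σ = 0.3: added SD 0.069; 0.3/√(0.0900 + 0.0048) = 0.97.

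Type I error stays at its nominal level.

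**3. Mean draw time differs by h hours between two groups or periods**
The shift in between-player SD units is hs/σ.
- h = 0.5: 0.04/0.3 = 0.13 to 0.075/0.2 = 0.38.
- h = 1: 0.08/0.3 = 0.27 to 0.15/0.2 = 0.75.

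**4. Wider range as a sensitivity check**
Let cortisol fall by 5% to 20% per hour, so the log slope is −ln(1 − fall), with the same σ. Here the standardising SD also includes the draw-time spread from step 2.
- Unrelated timing multiplies a true correlation by 0.72 to 0.99.
- A 1 h mean difference gives a spurious d of 0.17 to 0.80; a 0.5 h difference gives 0.08 to 0.40.
- For two equal groups totalling 149, the probability of a two-sided p < 0.05 is Φ(d√(149/4) − 1.96) + Φ(−d√(149/4) − 1.96). This is 18% to over 99% for 1 h, and 8% to 69% for 0.5 h.

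These rejection rates apply only if such a difference in mean draw time exists. They are not error rates to expect from the plan as written.

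**The case against.** The case against is strong on several points.

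- **No link between draw time and the comparisons is stated.** A reader might infer that draw time will imitate the effects the study looks for, for instance because players with classes or jobs take early slots. The article does not say how slots are allocated. Without a link, timing hides effects and does not create them. This stands, so the bias is stated only conditionally.
- **No dual-career biomarker contrast is specified.** A reader might also infer a false biomarker difference between dual-career and other players. The stated group factor is injured/ill versus healthy, so that inference has no stated analysis to rest on.
- **Large shifts are implausible.** A 2 h difference in means would give 0.16/0.3 = 0.53 to 0.30/0.2 = 1.5 SD, but it needs almost complete separation of two groups inside a 3 h window. Nothing in the article suggests this; 0.5–1 h is the range to consider.
- **The slope is outside knowledge, and clock time may not be what matters.** If level follows time since waking, players who are drawn earlier but also wake earlier need not have higher values. Within-player and assay variation would also lower the standardised shift. This stands, so the figures are illustrations.
- **Safeguards exist.** Sampling is in the morning only, after a rest day, and "The athletes will be tested under similar conditions every time" might be meant to include clock time. But the same sentence sets the time condition, and it is 3 h wide.
- **The full protocol may record draw times or fix slots.** That is possible, and the absence of such detail from an article is no fault. What remains is what the article does fix: the window, and a bivariate correlation, which by definition uses no covariate.

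**Conclusion.** The point holds in a limited form. A three-hour window combined with analyses that ignore draw time adds avoidable noise to the cortisol and ratio analyses and leaves room for confounding.

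On the assumed slope and spread, the noise is modest: a true correlation keeps about 84–97% of its value. A cortisol cut-off from the ROC analysis would be blurred too, since one player's value could differ by 21–36% between the ends of the window. The ROC sentence does not name its variables, so this applies if cut-offs are set for the biomarkers.

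Confounding, at about 0.13–0.75 SD for a 0.5–1 h difference in mean draw time, is a risk only if timing differs systematically by club, period or injury group. The article does not show that it will. Nor does it support a claim that draw time will produce false stress or dual-career findings. The effect is confined to the secondary aim, and this is a cheap improvement to the plan.

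**What to change.** **Blood biomarkers section.** Keep each player in the same narrow slot (for example 30–60 minutes) at every draw where feasible. Record the clock time of each draw and the player's waking time that day.

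**Statistical analysis section.** Replace the unadjusted bivariate correlation with a partial correlation or a regression adjusted for draw time or time since waking. Include the same covariate in the period and group comparisons of cortisol and the free testosterone:cortisol ratio. For any ROC cut-off on these variables, first bring values to a common reference time.

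**Cost.** Two recorded times per draw and somewhat tighter scheduling. Where slots cannot be held, the covariate alone should remove most of the problem, provided draw times overlap between the groups or periods compared. If a club or period is sampled at one time only, adjustment cannot separate the two. The times must be noted when blood is taken.

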### Statistical analysis

Statistical analysis will be performed using standard statistical software (SPSS V.27.0, IBM, Armonk, New York). Descriptive statistics will be used for all variables. Normality of data distribution will be assessed using the Shapiro-Wilk test. In case of non-normally distributed data, non-parametric statistics will be used, otherwise, the statistics for normally distributed data will be used. The data will be analysed using a logistic regression model to properly account for the dependency induced by the repeated observations over time within each subject. Main effect of all dependent variables on injury/illness occurrence will be studied using repeated measures analysis of variance (ANOVA) with time (preparation period vs competition period vs off-season period) as within factor, while group (injured/ill vs healthy) as between factor. Where significant effects will be found for group, time effects or two-way interactions, pairwise comparisons will be used to address the significant differences for each variable independently. For comparison of the groups, we will use independent t-test. The magnitude of effect for all dependent variables will be reported as partial eta squared (η^2^). In addition, *Cohens’ d* (ES) will be used to assess magnitude of difference between groups. Furthermore, regression analysis will be used to assess predictive power of individual parameters to identify injury/illness occurrence. For the correlation of subjective measures of stress with the objective measures, bivariate correlation will be used. Additionally, Bland-Altmann analysis will be used (low/high stress normative values) as previously recommended.^42^ Furthermore, receiver operating characteristic (ROC) curve analysis will be used for defining the cut-off values. Hypotheses will be accepted or rejected at p≤0.05.

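### The Shapiro-Wilk switch is likely to send several key load variables to unnamed non-parametric tests, where the planned group-by-period interaction would ordinarily be lost

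*Protocol article*

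**What the plan says.** All of the following stands in the Statistical analysis section of the protocol article unless noted.

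- The check: "Normality of data distribution will be assessed using the Shapiro-Wilk test".
- The consequence: "In case of non-normally distributed data, non-parametric statistics will be used". No non-parametric method is named.
- The planned two-factor analysis: "repeated measures analysis of variance (ANOVA) with time (preparation period vs competition period vs off-season period) as within factor", with "group (injured/ill vs healthy) as between factor".
- The interaction is part of that plan: "Where significant effects will be found for group, time effects or two-way interactions, pairwise comparisons will be used". Partial eta squared is to be reported for all dependent variables.
- A separate model for the weekly data: "The data will be analysed using a logistic regression model to properly account for the dependency induced by the repeated observations over time".
- Table 1 lists six weekly load and stress variables: training hours, competition minutes, academic hours, work hours, sleep, and "Perceived stress on scale 1–10".

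The section does not say whether normality is judged on weekly values, period means, group-by-period cells or residuals.

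**The concern.** A significance test of normality becomes stricter as the sample grows, and this cohort is large enough to detect departures that matter little for an analysis of means. Several of the study's variables cannot be close to normal by construction. Players without a dual career are eligible, so academic and work hours contain structural zeros. Competition minutes are bounded and are zero for players who did not play. A weekly stress score is a coarse rating.

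When the switch fires, the section pulls two ways. It still promises follow-up of interactions and partial eta squared, yet it leaves the analysis that produces them. The interaction is the only ANOVA term that asks whether load changes differently over the season in injured/ill and healthy players. The variables most exposed include academic and work hours, the dual-career loads named in the primary aim. Because the data choose the method one variable at a time, results would also not be comparable across loads.

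**Working it through.** **1. The plan's own figures.** The article gives no figure for the normality rule, so the only ones to reproduce are the sample sizes (Participants and sample size).
- With OR = 1.78, p = 1.78/2.78 = 0.640 and p − 0.5 = 0.140, which matches the stated effect size of 0.14. An exact two-sided sign test then has power 0.905 at n = 134 (0.885 at n = 133).
- Drop-out: 134/(1 − 0.10) = 148.9, so 149.
- The abstract states 200.

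The figures reproduce and serve here only to set the range n = 134, 149, 200.

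**2. How often the switch fires.** Shapiro-Wilk at 0.05 was simulated at those three sizes. The article gives no distributions, zero shares or period lengths, so all of these are assumptions: 50% zeros for academic hours, 70% zeros for work hours, bounded competition minutes, sleep rounded to half hours, and periods of 6, 34 and 6 weeks (6 + 34 + 6 = 46, the stated season length).

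| Variable | Single-week values | Player means over 6 or 34 weeks |
|---|---|---|
| Academic, work, competition | about 100% each | 98–100% each |
| Stress, 1–10 | about 100% | 8–27% if player means are near normal; 100% if right-skewed |
| Sleep | about 100% | 4–10% |
| Training hours, near normal | 9–11% | 2–6% |

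On weekly values five of six variables almost surely fail. On period means it is three of six, or four if stress is skewed. A second simulation of near-normal stress period means gave about 6%.

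**3. Sensitivity to the assumptions.**
- Zero share at n = 134, with the non-zero hours drawn from a normal with mean 20 and SD 8: 96% rejection with 10% zeros and 100% with 20% or more.
- Skewness alone at n = 149: 0.25, 0.5, 0.75 and 1.0 give 18%, 58%, 93% and 100%.
- Log-normal biomarkers at n = 134: log-SD 0.2, 0.3 and 0.4 give 68%, 95% and 100%.

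**4. Chance firing.** If each cell is tested separately, truly normal data fail at least once with probability 1 − 0.95³ = 0.143 for three periods, or 1 − 0.95⁶ = 0.265 for six group-by-period cells, treating the tests as independent.

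**5. What remains after the switch.** Mann-Whitney compares the two groups and Friedman compares the periods. Neither compares the change over periods between groups, and neither yields partial eta squared.

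**6. Whether the switch is needed.** The interaction F-test was simulated without any interaction at N = 149, with injured/ill shares of 0.3, 0.6 and 0.8 and 2000 runs each. The Monte Carlo standard error is √(0.05 × 0.95/2000) = 0.005.

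| Data | Type I error |
|---|---|
| Academic hours, zero-heavy | 0.055–0.065 |
| Competition minutes, bounded | 0.048–0.058 |
| Log-normal | 0.053–0.060 |

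The highest value is about three standard errors above 0.05, so there may be some inflation for zero-heavy hours, but it is small. Non-normality alone gives little reason to give up the interaction at this sample size.

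**The case against.** The strongest reply is that the forecast depends on things the article does not state.

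- **Unit.** The only analysis with a group-by-period interaction uses three periods, so weekly reports would normally be averaged first. A reader might infer that nearly every load and stress variable will fail. That fits single-week values only; on period means, training, sleep and near-normal stress mostly pass. The text also does not say that raw values are tested.
- **Loss of the interaction.** A reader might infer that the plan leaves the interaction untested. It does not say so: it still commits to following up interactions, it names no non-parametric method, and rank-based factorial methods exist. A condensed article may leave the choice of method to an analysis plan that is not shown, so the missing name is not a fault in itself.
- **Primary aim.** A reader might infer that the main analysis fails. Logistic regression, with injury or illness as the outcome, addresses the aim most directly, and nothing in the text makes it depend on normally distributed predictors. The ANOVA, with load as the response, is supportive.

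These replies stand, and they limit the point. They do not remove it. The switch itself is written in the article, it fires for academic, work and competition load under either unit of analysis, and the tests it ordinarily leads to cannot deliver what the same section promises.

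**Conclusion.** The point holds in limited form. At 134 to 200 athletes, the rule is likely to move academic, work and competition load off the planned ANOVA (about 98–100% of simulated samples, even as period means), and weekly stress and sleep too if single weeks are tested. For those variables the group-by-period interaction and partial eta squared would ordinarily be lost, and methods would be mixed across variables. There is little gained in return, since the planned interaction test keeps a type I error of about 0.05–0.065 on such data.

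The percentages rest on assumed zero shares, shapes and period lengths. The conclusion for the zero-heavy loads is robust to the zero share, with 96% rejection already at 10% zeros; for stress, sleep and the biomarkers it depends on the unit tested and on skewness. The logistic regression is unaffected. This should be changed but is not fatal. Confidence is moderate.

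**What to change.** Delete the normality switch. State in advance one group-by-period model with interaction for every variable. The planned ANOVA would do; a linear mixed model in SPSS is preferable because it can keep players who miss a period, and the article itself expects 10% drop-out.

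- Log-transform the hormones and the testosterone-to-cortisol ratio.
- Use robust or athlete-level bootstrap standard errors for the zero-heavy variables.
- State the unit of analysis (period mean or week).
- Limit distributional checks to residuals, without letting them change the model.
- If the mixed model is chosen, report the group-by-period contrasts with confidence intervals in place of partial eta squared, which belongs to the ANOVA.

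The cost is rewording and slightly more analysis work. No data collection or sample size changes.

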## Methods and analysis

### Study design

The study is designed as a prospective cohort study. All measurements will be conducted over a single handball season, lasting from July 2022 to June 2023 (a total of 46 weeks), with weekly reporting (table 1) and three to five biomarker sampling timepoints (figure 1). We used the Standard Protocol Items: Recommendations for Interventional Trials (SPIRIT) checklist when writing our report.^37^

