### Assessment and outcomes

#### Oslo Sports Trauma Research Centre Questionnaire on Health Problems

The Oslo Sports Trauma Research Centre Questionnaire on Health Problems (OSTRC) is a tool to capture and monitor health problems longitudinally in athletes. It consists of 18 questions, which are answered for the past 7 days. The first four questions are to determine the severity of the health problem, while the rest are to further classify the health problem, such as type and anatomical location of the problem.^40^ As per previously established protocol, the athletes in our study will self-report their health status weekly with the help of a physiotherapist, while using the OSTRC questionnaire.^40^ The athletes with reported health problem will be contacted by a medical professional to clinically verify the reported health case.

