#### Weekly load and stress questionnaire

The teams will weekly report training and competition load for each athlete, while academic (educational activities, including lectures, exams and studying) and work load (a part-time or full-time job besides playing sports) for the past 7 days will be reported by the athletes themselves. Competition load will be reported in minutes for each game played in the past week, while training, academic and workload will be reported in hours. The athletes will additionally report average hours slept per day over the past week and rate their perceived overall stress of that week on the scale 1–10.

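### For injuries, handball hours are both the load under study and the opportunity to be hurt; with no exposure denominator and no lag, load cut-offs cannot be read as tolerance limits

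*Protocol article*

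**What the plan says.** The Weekly load and stress questionnaire section fixes how sport load is measured: "The teams will weekly report training and competition load for each athlete", and "Competition load will be reported in minutes for each game played in the past week, while training, academic and workload will be reported in hours". Table 1 agrees ("Training load in hours"). Sport load is therefore a duration and nothing else.

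Table 1 gives the outcome as "Weekly health problems (acute and overuse injuries, illnesses), measured as prevalence and incidence and severity as OSTRC-severity score and time-loss days", without a denominator for incidence. On the health questionnaire the article says: "It consists of 18 questions, which are answered for the past 7 days". The load report covers the past week too, so exposure and outcome share one window. Follow-up is "lasting from July 2022 to June 2023 (a total of 46 weeks), with weekly reporting".

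Part of the primary aim is "how much of a variation in the athlete’s load leads to an occurrence of an injury/illness". To reach it, the Statistical analysis section names a logistic regression for repeated observations, an ANOVA ("Main effect of all dependent variables on injury/illness occurrence will be studied using repeated measures analysis of variance (ANOVA") with period as within factor and injured/ill against healthy as between factor, t-tests, further regression for predictive power, and ROC curves for cut-offs. It names no hours at risk, no rate and no lag.

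**The concern.** A player can only have a handball injury while playing or training. If every hour carries the same risk, a week with more hours still has more injuries, and injured weeks or players show more hours. A model of injury occurrence on hours cannot tell this from load making the athlete more vulnerable.

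The shared 7-day window adds a distortion in the other direction. A player hurt early in the week trains less for the rest of it, so the injury lowers the recorded load.

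What is at stake is the part of the primary aim about how much load an athlete can withstand before injury. An ROC cut-off on weekly hours would probably be read as a tolerance limit, although it could reflect opportunity, hours lost to the injury, or a mixture of both.

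**Working it through.** **The plan's own figures.** The article gives no effect size for sport load. Its planning odds ratio of 1.78 is for high against low academic stress, so it is no benchmark here. Its adjusted sample size, 134/(1 − 0.10) = 148.9, so 149, is used below only as the number of players.

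**Inputs.** From the article: load in hours or minutes, outcome over the past 7 days, 46 weeks, 149 players. Assumed, because the article gives neither: 3 to 15 injuries per 1000 player-hours, and 2 to 12 handball hours per week.

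**Step 1: opportunity alone.** With constant risk r per hour, the weekly probability of injury at h hours is p = 1 − exp(−rh). The odds are exp(rh) − 1, so

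OR = (exp(r·h1) − 1) / (exp(r·h0) − 1).

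| Hours compared | r = 3/1000 | r = 15/1000 |
|---|---|---|
| 12 vs 8 | 0.0367/0.0243 = 1.51 | 0.1972/0.1275 = 1.55 |
| 10 vs 5 | 0.0305/0.0151 = 2.02 | 0.1618/0.0779 = 2.08 |
| 12 vs 2 | 0.0367/0.0060 = 6.09 | 0.1972/0.0305 = 6.48 |

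No row contains any effect of load on risk per hour. The result hardly depends on the assumed rate; it follows the ratio of hours.

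**Step 2: the planned type of model.** A simulation of 149 players over 46 weeks (60 runs) used a constant 8 injuries per 1000 h and mean weekly hours of 12 in preparation, 10 in competition, 2 in the off-season and 3 in breaks, all assumed. Results per +5 h per week:

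- logistic regression on weekly hours: OR 1.85, p<0.05 in 100% of runs;
- the same with period terms: OR 1.71;
- without off-season or break weeks: OR 1.59;
- complementary log-log with log(hours) as offset: ratio 1.00, p<0.05 in 7% of runs.

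Low-handball weeks enlarge the artefact but do not create it, and adjusting for period does not remove it.

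**Step 3: the injury cuts that week's hours.** If the event falls at a uniformly distributed point in the week and no hours are logged after it (assumed), the logistic OR per +5 h becomes 0.40 for injury only and 0.34 with 5% weekly illness added. High load now looks protective. An offset without a lag does not repair this: the ratio is 0.16 for injury only.

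**Step 4: illness.** With 5% weekly illness unrelated to hours and no shortening, the logistic OR is 0.99, so there is no opportunity artefact. An hours offset would create a false ratio of 0.47. Pooling such illness with injury dilutes the artefact of step 2 to 1.42 (5% weekly) or 1.29 (10% weekly).

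**Step 5: matches and training.** If a match hour carries k times the risk of a training hour (assumed), 10 h training plus 1 h match against 10 h training gives (10 + k)/10 = 1.5, 2.0 or 3.0 for k = 5, 10 or 20. Total hours alone therefore do not describe exposure; the match share matters as well.

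**The case against.** The strongest objection is that risk per player-week is a legitimate target. A club planning a week may want the total risk, opportunity included. That stands. But the article does not say which target it means, and a threshold for what an athlete can withstand is not a weekly total.

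It is also fair that a journal article condenses a plan, and that incidence might be given a denominator elsewhere. This has less force because the article fixes the methods: ROC curves on hours and comparisons of injured with healthy players have no place for hours at risk.

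A third objection is that the injury itself shortens same-week hours used as an offset. In a rate model, hours up to the injury are the correct person-time. The trouble arises when the same shortened hours are also the predictor, which a lag avoids.

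A reader might infer more than the document supports:

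- *Higher load will look harmful.* The direction is not determined; step 3 gives the opposite sign.
- *Low-handball weeks count as equally at risk.* No section says so, and the ANOVA treats the off-season as its own level. The weight of the point lies on the logistic regression, the ROC analysis and the injured-against-healthy comparison of hours.
- *Training outside the club goes unrecorded.* The article has the teams report load for each athlete and does not limit this to club sessions.
- *The whole load analysis is affected.* The opportunity argument does not reach illness, academic load, work load, sleep or perceived stress.

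**Conclusion.** The point holds for sport load and injury. As described, the analyses can give a positive association from opportunity alone, with an odds ratio of about 1.5 to 2.1 for the moderate contrasts of 12 against 8 h and 10 against 5 h. They can also give a reversed one when injury reduces the hours of the same week. Which of the two dominates cannot be told from the article, so neither the coefficient nor a cut-off on hours can be interpreted as load tolerance. The sizes rest on assumed injury rates, weekly hours and a constant risk per hour; the mechanism rests only on the units of load, the shared window and the named models. This is a change that should be made. It does not question the sample size or the collection of the other loads.

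**What to change.** Analyse injury and illness separately, and state for each whether the target is risk per handball hour or per player-week.

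- **New acute handball injuries:** a repeated-measures rate model (Poisson or complementary log-log) with the log of that week's handball hours as offset, load of the preceding week or weeks as predictor, and match share as covariate. Leave out weeks with zero handball exposure from this model only.
- **Overuse injuries and illness:** keep all weeks and model risk per player-week, also on preceding-week load, because a health problem of either kind can reduce the hours of its own week. Use no hours offset for illness.
- **Weekly injury risk and cut-offs:** if weekly risk is also reported for injuries, label it as including opportunity. Derive ROC cut-offs from preceding-week load. The lag removes the reversal, but not all of the opportunity effect where a player's hours are similar from week to week, so the label should apply to these cut-offs as well.

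The cost is some added analysis work, loss of the first week or weeks to the lag, and possibly a smaller apparent effect of load. Hours, minutes and the division into acute and overuse injuries are already in the plan; the model also needs to know that an acute injury arose in handball, which could be settled when cases are clinically verified.
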